# LIST OF ABBREVIATIONS

AMTSL= Active management of third stage of labour

ACOG= American college of obstetricians and gynaecologists

ATP= Adenosine tri phosphate

DCC= Delayed cord clamping

EDTA= Ethylenediaminetetraacetic acid

ERC= Ethical review committee

EPO= Erythropoietin

HB= Haemoglobin

HCT= Haematocrit

ICC = Immediate cord clamping

IVH= Intraventricular haemorrhage

KDHS= Kenya Demographic and health survey

KNH= Kenyatta National Hospital

MCV= Mean corpuscular volume

MCHC= Mean corpuscular haemoglobin concentration

MCV= Mean corpuscular volume

NEC= Necrotizing enterocolitis

PCV= Packed cell volume

PPH = Post partum haemorrhage

RBC= Red blood cell

RCT= Randomized controlled trial

UON= University of Nairobi

WHO= World health organization

# OPERATIONAL DEFINITIONS OF TERMS

- **Anaemia:** Hb concentration more than two standard deviations (SD) below the mean of similarly aged infants from an iron-supplemented reference population
- **Anaemia in pregnancy:** defined as Hb < 11 g/dl Ref sources
- **Clinical jaundice:** yellowish discolouration of the skin, and/or conjunctiva.
- **Delayed cord clamping (Late cord clamping)**: clamping the umbilical cord between 60-120 seconds after birth. Ref sources
- **Early cord clamping/ Immediate cord clamping:** Clamping of the umbilical cord within 30 seconds of birth.
- **Neonatal Haematocrit:** Range of normal between 45-65%
- **Placental transfusion**: The transfer of residual placental blood to the baby during the first few minutes of age.
- **Polycythaemia:** Haematocrit levels >2SD above the normal value for gestational age.
- **Preterm infant:** infant born less than 37 weeks’ gestation
- **Primary post-partum haemorrhage:** blood loss of 500mls after vaginal delivery or 1000mls after cesarean delivery; within in the first 24 hours after delivery.
- **Umbilical cord milking:** the unclamped umbilical cord is grasped and blood is pushed toward the infant several times before it is clamped to auto infuse blood into the preterm neonate

#

# ABSTRACT

**Background:** The placenta is a useful reservoir of fetal blood that can serve to alleviate anaemia of prematurity, prevalent in almost all premature neonates(1). Immediate cord clamping is a routine practice worldwide despite current evidence on the benefits of providing placental transfusion to the new born(2). Umbilical cord milking and delayed cord clamping are two such strategies providing for placental transfusion. Major obstetric and gynaecological societies are now recommending delayed cord clamping(3,4). Umbilical cord milking is a cost effective intervention and can be considered for faster placental transfer when delayed cord clamping cannot be performed such as when a neonate requires resuscitation. The findings of this study will inform strategies to reduce neonatal anaemia in a country that is one of 15 responsible for over 2/3^rd^ the world’s preterm births and its subsequent complications specifically anaemia(5).

This study aims to evaluate that umbilical cord milking is comparable in benefits to delayed cord clamping and can be beneficial to premature neonates where every second after birth is essential.

**Objective:**  To determine the effects of umbilical cord milking versus delayed umbilical cord clamping on selected haematological and clinical parameters in preterm neonates.

**Methodology:** Randomized controlled trial, single blind. Mother-baby pairs at premature gestation (<37weeks) who meet the selection criteria, will be randomized to either Umbilical cord milking (n=140) or Delayed cord clamping (n=140). UCC will be performed≥60 seconds after delivery and UCM will be performed 4times.

The primary outcomes of the study will be haemoglobin and haematocrit levels determined 24 hours after birth. The secondary outcomes will be neonatal jaundice and maternal primary postpartum haemorrhage.

**Study setting:** Kenyatta National hospital labour ward, maternity theatre and neonatal intensive care unit.

**Data collection tool**: Interviewer administered questionnaire will be used by the principal investigator and 2-research assistants.

**Analysis plan**: Levels of haemoglobin and haematocrit of newborn infants following umbilical cord milking will be compared to those of newborns who undergo delayed cord clamping using unpaired students T- test and a P value <0.05 for significance. Prevalence will be compared using proportions and chi squared test of independence. Measurements of excess risk will be estimated using relative risk at 95%confidence interval that excludes the null value will be considered significant. Intention to treat analysis will be used.

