# Justification

Neonatal mortality is the leading cause of mortality in children under the age of five years in Kenya. Nearly 35% of under-5 deaths occurred during the neonatal period; 1/3^rd^ of all neonatal deaths are due to severe infections, followed by birth asphyxia, preterm births and congenital anomalies.

Preterm neonates are at risk of developing complications that will affect their chances of survival. The extent to which they develop complications strongly depends on the quality of care they receive at birth. In a preterm neonate already predisposed to such disadvantages the extra blood received from the placenta can give a boost to their already disadvantaged status.

The additional blood obtained through placental transfer can improve haemoglobin levels at birth, stabilize neonatal transition, reduce rates of blood transfusion and increase neonatal iron storage in preterm neonates.

Delayed cord clamping is recommended by all major obstetric societies but less information exists on umbilical cord milking.UCM is potentially an effective, faster placental transfer strategy when DCC cannot be performed such as when a neonate requires resuscitation or to expedite delivery in the advent of maternal complications.

Directly comparing the recently recommended practice of delayed cord clamping to umbilical cord milking before clamping has potential to prove beneficial for the neonates in question, as well inform obstetric practice and policy on placental transfusion in a maternity with heavy workloads.

If this study shows that umbilical cord milking has the same benefits if not more to the preterm neonate, this can give clinicians confidence to implement and use umbilical cord milking as part of their management plan for preterm neonates in a maternity with a high turnover of patients. It can also be used to advocate for policies to introduce umbilical cord milking as a routine practice to be done on all preterm neonates. Currently no specific protocol with regards to placental transfusion exists in Kenyatta national hospital.

Most studies have been done in the developed countries; this study seeks to replicate similar or better outcomes for haemoglobin levels amongst a population with higher incidence of anaemia.

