# Study objectives

Research question:

Is there a difference in haemoglobin, haematocrit and neonatal jaundice between preterm infants who will undergo umbilical cord milking versus delayed cord clamping?

Broad objective:

To determine the effects of umbilical cord milking versus delayed cord clamping on haemoglobin, haematocrit, and neonatal jaundice of preterm neonates.

Primary objectives:

Among preterm neonates at 28-36 weeks who will undergo umbilical cord milking versus delayed cord clamping at vaginal or caesarean delivery, to:

1. Determine and compare the mean haemoglobin and haematocrit values at 24 hours of life.

Null hypothesis: There is no difference in the mean haemoglobin and haematocrit values 24 hours after birth comparing pre term neonates delivered at 28-36 weeks who will undergo umbilical cord milking versus delayed cord clamping.

1. Determine and compare the incidence rate of neonatal polycythemia at 24 hours of life.

Null hypothesis: There is no difference in the incidence rate of neonatal polycythemia at 24 hours after birth comparing pre term neonates delivered at 28-36 weeks who will undergo umbilical cord milking versus delayed cord clamping.

1. Determine and compare the incidence rate of neonatal jaundice within the first week of life.

Null hypothesis: There is no difference in the incidence rate of neonatal jaundice within the first week of life comparing pre term neonates delivered at 28-36 weeks who will undergo umbilical cord milking versus delayed cord clamping.

Secondary objectives:

Among preterm neonates at 28-36 weeks who will undergo umbilical cord milking versus delayed cord clamping at vaginal or caesarean delivery, to:

1. Determine and compare the incidence rate of neonatal anaemia within the first 24 hours of life.
2. Determine and compare the incidence rate of maternal primary post partum haemorrhage within 24 hours of delivery.

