### Benefits

If umbilical cord milking is found to be more beneficial for the premature, they will gain by receiving the best obstetric practice especially in scenarios where time is of importance and neonatal resuscitation is required. The findings will benefit the participants in case the positive findings are implemented at a later date. The information learnt from this study may in future help the participants and others.

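### The Abstract and Justification aim at comparability, but every planned test is of no difference and no margin is set, so a non-significant result could be read as the same benefits

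*Protocol*

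**What the plan says.** All references are to the Protocol; a statistical analysis plan is not at hand.

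- **Aim (Abstract, Background):** "This study aims to evaluate that umbilical cord milking is comparable in benefits to delayed cord clamping".
- **Intended use (Justification):** "If this study shows that umbilical cord milking has the same benefits if not more to the preterm neonate", then "this can give clinicians confidence to implement and use umbilical cord milking as part of their management plan for preterm neonates". The same paragraph looks to policies that would make milking routine for all preterm neonates.
- **Research question (Study objectives):** "Is there a difference in haemoglobin, haematocrit and neonatal jaundice between preterm infants", comparing milking with delayed clamping.
- **Primary null (Study objectives):** "There is no difference in the mean haemoglobin and haematocrit values 24 hours after birth". The polycythaemia and jaundice nulls have the same form.
- **Tests (Abstract, Analysis plan):** means are compared "using unpaired students T- test and a P value <0.05 for significance". Proportions are compared by a chi-squared test. For relative risks the rule is "95%confidence interval that excludes the null value will be considered significant". The Data Analysis section puts all tests at the 5% level and mentions odds ratios from regression.
- **Sample size:** sized to detect a difference of 0.7 with SD 2, 80% power and z = 1.96. This gives 128 per arm, and 280 in total after an allowance of 10%.

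No section gives a non-inferiority or equivalence hypothesis, a margin, or a rule for concluding that the two methods are comparable.

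**The concern.** A test of no difference can end in two ways. It rejects equality, or it fails to reject. Failing to reject is not evidence of equality, because the data may also be compatible with a deficit large enough to matter. A comparability claim needs a margin fixed in advance and an interval that excludes any deficit larger than it.

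Here the two parts of the plan do not meet. The Abstract and Justification want to be able to say that milking does as well as delayed clamping. The hypotheses, tests and sample size can say only whether the two differ. If the result is non-significant, the stated aim invites the conclusion that the benefits are the same, and the Justification links that conclusion to routine practice. A real loss of haemoglobin under milking could then go unrecognised.

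This cannot simply be left to an analysis plan, since the protocol itself states the aim, the nulls, the tests and the basis of the sample size.

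**Working it through.** **Inputs.** From Sample Size: SD = 2, d = 0.7 (taken as g/dl of haemoglobin), 1:1 allocation, z = 1.96 and 0.84, 140 per arm. Evaluable number after 10% loss: 140 × 0.9 = 126 per arm. True deficits other than 0.7, and all margins, are assumptions, because the protocol gives none.

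**1. The plan's own figure.** n = 2 × SD² × (0.84 + 1.96)² / d² = 2 × 4 × 7.84 / 0.49 = 128 per arm. This reproduces. The total is 256, and 256 × 1.1 = 281.6, close to the stated 280. It is the size for detecting a difference.

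**2. Precision.** SE = 2 × √(2/126) = 0.252. The 95% CI half-width is 1.96 × 0.252 = 0.49 g/dl (0.490 at 128 per arm).

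**3. Chance of a non-significant result when milking is truly worse by δ.** P ≈ Φ(1.96 − δ/SE); the other tail is negligible.

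| True deficit (g/dl) | 1.96 − δ/0.252 | P(p > 0.05) |
|---|---|---|
| 0.4 | 0.37 | 64% |
| 0.5 | −0.02 | 49% |
| 0.7 | −0.82 | 21% |

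**4. What such a result may still contain.** An observed deficit between 0.7 − 0.494 = 0.21 and 0.49 is non-significant, yet its 95% interval reaches a deficit of 0.7, the difference the trial is sized to detect. If the true deficit is 0.5, this happens with probability Φ((0.5 − 0.206)/0.252) − Φ((0.5 − 0.494)/0.252) ≈ 0.37.

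**5. What the same sample could do with a margin M.** Take a true difference of zero and a one-sided 2.5% level (lower limit of the two-sided 95% CI above −M). Then power = Φ(M/SE − 1.96) and n = 2 × SD² × (1.96 + 0.84)² / M², computed with unrounded z.

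| Assumed margin (g/dl) | Power, 126 per arm | Evaluable n per arm for 80% |
|---|---|---|
| 0.7 | 79% (80% at 128) | 129 |
| 0.5 | 51% | 252 |
| 0.4 | 35% | 393 |

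At a margin of 0.5, allowing for 10% loss gives 252/0.9 = 280 per arm, or 560 in total, twice the plan.

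**6. Departures from allocation.** The Intervention groups section sends some newborns in both arms to early clamping whatever their allocation. The Abstract specifies intention to treat. If a fraction f of each arm is handled identically and contributes no difference, the expected difference becomes (1 − f) × δ. The documents do not give f. As an illustration, f = 10% turns 0.7 into 0.63. The pull is towards zero, which favours a comparability claim.

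**The case against.** The strongest reply is that the operative sections agree with one another. The Abstract's objective, the research question, the nulls, the tests and the sample size all describe one difference trial. Comparability appears in a background sentence and in a conditional sentence of the Justification. This stands: the fault is a mismatch between the stated aim and the formal design, not an error within that design.

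A reader might infer more than the documents support:

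- **That a non-significant result will be reported as comparable.** No section says so. The aim makes that reading foreseeable, no more.
- **That the trial can support none of its intended conclusion.** The planned test can support superiority, which the Justification also contemplates and which the opening of the Benefits sentence assumes. Only the claim of sameness lacks support.
- **That the t-test is the only analysis.** A chi-squared test, relative risks and regression are also planned, though all are judged against no effect.
- **That 280 infants are too few.** This depends on the margin. At 0.7 the size is about right; at 0.5 it is not.
- **That 0.7 is the natural margin.** Sample Size defines it as the expected difference from an earlier study, not as a loss that clinicians would accept.

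It is also fair to say that no section calls a deficit of 0.4 or 0.5 g/dl important. At the planning difference of 0.7, the 21% is essentially the planned type II error. But a one-in-five chance of missing the planning difference is acceptable when the result is reported as no difference shown, and not when it is offered as evidence of sameness.

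**Conclusion.** The point holds as a mismatch. The comparability aim in the Abstract and Justification cannot be established by the nulls, tests and sample size that the protocol sets, and there is no margin against which to judge it. A non-significant result could be read as the same benefits when the interval extends about 0.49 g/dl either side of the estimate. The figures assume SD 2, 126 evaluable infants per arm, a normal approximation, and true deficits and margins chosen for illustration.

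A related limit concerns the population. Need for neonatal resuscitation is an exclusion criterion, yet the Benefits section sees the gain "especially in scenarios where time is of importance and neonatal resuscitation is required". The trial will not estimate the effect of milking in those infants, so no conclusion about them follows. This is a matter of generalisability and does not make the mismatch itself worse.

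**What to change.** 1. Make the milking minus delayed-clamping difference in mean haemoglobin, with its two-sided 95% confidence interval, the primary result.
2. State that p ≥ 0.05 will be reported as no difference shown, not as comparability.
3. Then choose one route:
   - **(a)** Reword the Abstract and Justification so that the aim is to test for a difference. This needs no margin.
   - **(b)** Fix a clinically justified margin before any data are seen. Claim comparability only if the lower confidence limit lies above minus that margin, and superiority only if it lies above 0. Both can be read from the one interval without an alpha penalty. The timing matters because Appendix IV has an unblinded statistician monitoring continuously.
4. Under (b), add an analysis of infants who received the assigned intervention beside intention to treat, because early clamping in both arms pulls the latter towards zero. It is supportive only, since it gives up the protection of randomisation.
5. Limit the conclusion to infants not needing resuscitation, and to haemoglobin unless the other primary outcomes are given their own rule.

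**Cost.** Route (a) takes a few sentences. Route (b) takes a paragraph and a margin the sponsor must defend. It needs essentially no extra infants if 0.7 can be justified clinically, but about 560 in total for 80% power at 0.5. Under either route the sponsor may be unable to claim comparability.

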# Introduction/background

Over the decades, immediate cord clamping has become routine practice in majority of delivery facilities. This practice was an adjunct to Active management of third stage of labour in an initiative package to reduce post partum haemorrhage and was adopted worldwide. Immediate cord clamping is no longer considered a beneficial component of Active management of third stage of labour and may even be harmful to mothers and babies(6). Immediate cord clamping may deprive the neonate of placental respiration and transfusion resulting in complete asphyxia pending the lungs becoming functional, and 30-50% of the neonate’s natural blood volume. A neonate that receives full placental transfusion will have enough iron stores while immediate clamping may lead to anaemia during the first year of life(7). Several studies are now focusing on the effect of placental transfusion to the new born using two strategies which are Delayed cord clamping and Umbilical cord milking.

The American college of obstetricians and gynaecologists recommend a 30-60 second delay in umbilical cord clamping for all preterm deliveries(8). It is an extremely effective method of enhancing arterial oxygen content, increasing cardiac output and improving oxygen delivery. For preterm infants benefits include better establishment of red blood cell volume and decreased need for blood transfusion as well as lowering incidence of intraventricular haemorrhage and necrotizing enterocolitis(8).

A Preterm infant has impaired hemodynamic transition and needs an alternate method to provide placental transfusion while allowing for resuscitation(9). Umbilical cord milking is appropriate when delayed cord clamping cannot be performed to effect placental transfer.

A prevalent quandary seen in a high percentage of preterm neonates is anaemia which has major adverse health, social and economic development consequences. The placenta is a useful reservoir of fetal blood that could prove useful to the neonate. It is estimated that globally 273 million children under 5 years of age were anaemic in 2011, and about 42% of these cases were attributable to iron deficiency anaemia(10). Children are particularly vulnerable to iron deficiency anaemia because of their increased iron requirements during periods of rapid growth, especially in the first 2 years of life.

Children with iron deficiency are more likely to have delayed psychomotor development, and when they commence school, they are more likely to have impaired psycho motor performance equivalent to a 5–10-point deficit in intelligence quotient(4). Both epidemiological and experimental data suggest that when these impairments occur at an early age, they may be irreversible, even after repletion of iron stores, thus reinforcing the importance of interventions that may increase placental transfer to the neonate.

# LITERATURE REVIEW

### Introduction and epidemiology

Ensuring healthy lives and promoting well being for all and at all ages is part of the sustainable development goals adopted by the international community in the year 2015(11). One of the targets is to end preventable deaths of newborns and children under 5 years of age by 2030 with all countries aiming to reduce neonatal mortality to as low as 12 per 1000 live births and under 5’s to as low as 25 per 1000 live births(11). Pre term birth is the single most important cause of neonatal deaths and second leading cause of death under 5’s(12).

The global Preterm birth rate is estimated at 11.1%(5). Out of 15 million pre term births each year 1.1 million die from preterm birth complications. More than 60 percent of worldwide preterm births occur in sub Saharan Africa and south East Asia(5). The estimated national rate of preterm birth for Kenya is 12.3% that is approximately 193,000 children born prematurely and Kenya is amongst 15 countries that account for two third of the world’s pre term births(5,13).

In a 2011 study, Wagura found the pre term birth rate to be 18.3% at Kenyatta national hospital(14). Statistics show approximately 648 neonates die annually due to prematurity related complications at Kenyatta National Hospital.

### Anaemia of prematurity

Pre term infants are at risk of developing short term and long term complications that result from functional and anatomic prematurity during the neonatal period. One such complication is anaemia of prematurity(1).

During embryogenesis, fetal erythrocytes are produced in the yolk sac for the first few weeks and by the end of the first trimester the fetal liver becomes the primary site of erythropoiesis. By approximately 32 weeks gestational age the liver and the bone marrow are responsible for erythropoiesis until finally by week 40 of gestation the bone marrow is solely responsible. Erythropoietin being the most important erythropoietic growth factor is initially produced in the fetal liver and as gestation advances production shifts to the kidneys. Stimulation is in response to anaemia and tissue hypoxia. The fetal liver has a higher threshold for stimulation compared to the fetal kidneys consequently production of erythropoietin is blunted in an anaemic premature whose primary site is the fetal liver. Additionally Iron and other substrates are required to mount a response to erythropoietin which may be insufficient in premature neonates(15).

The average life span of a neonatal RBC is approximately 60 days(16) ranging from one half to two third that of an adult RBC (120 days). This is due to reduced levels of intracellular ATP, enzyme activities and carnitine. The RBC has increased susceptibility to fragmentation of the red cell membrane and increased susceptibility to lipid peroxidation(17).

